### Internal pilot and stopping rules

To ensure the success of the trial, screening data will be kept on the GHD Reversal Trial database on the number of early re-tests, GHD reversers and recruits. No patient identifiable information will be collected at this stage. These data will be analysed and presented as part of the progress report for the trial steering committee (TSC). According to published standards, Amber and Red ‘Stop/Go’ criteria have been agreed with the Funder. Time points are calculated from first centre opening. Three Stop–Go criteria measurable in the first 12 months of the trial were identified as critical steps for the trial’s successful recruitment (see Table 1).

**Table 1 Tab1:** GHD Reversal Trial Stop/Go criteria

Criterion	Threshold	Risk status
Sites open		
At 6 months	< 6 sites	AMBER
At 12 months	< 12 sites	RED
GHD reversal rate (i.e. size of pool of eligible patients)		
After 20 patients tested	< 20% (*n* = 4)	AMBER
After 40 patients tested	< 25% (*n* = 10)	RED
Number of eligible (GHD reversed) patients recruited		
At 6 months	< 15	AMBER
At 12 months	< 30	RED

### Planned interim analysis

Interim analyses of safety and efficacy for presentation to the independent DMC will take place during the trial. The committee will meet prior to trial commencement to agree the manner and timing of such analyses but this is likely to include the analysis of the primary and major secondary outcomes and full assessment of safety (SAEs) at least at annual intervals. Criteria for stopping or modifying the trial based on this information will be ratified by the DMC. Details of the agreed plan will be written into the SAP.

### Planned final analyses

The primary analysis for the trial will occur once all participants have either fulfilled the near FH definition (growth rate of < 2 cm/year and have reached a bone age of 14 years (females) or 16 years (males)), have completed the 36-month assessment or have withdrawn from the study or been lost to follow-up and corresponding outcome data have been entered onto the trial database and validated as being ready for analysis. All other outcome measure analyses will be undertaken when the final participant (as defined above) reaches their 36-month assessment.

### Health economics analysis

The health economics analysis has two specific aims. The first is to assess the cost-effectiveness of GH discontinuation in the early re-testing scenario by estimating the cost per percentage of children achieving TH of GH − compared to GH + over a 12-month period, and the second is to assess the cost-effectiveness of the new care pathway (early re-testing) compared to traditional care (late re-testing).

To assess the cost-effectiveness of no GH therapy (GH −) compared to GH therapy (GH +) in patients with GHD reversal, a cost-consequence analysis will initially be reported, describing all the important results relating to resource use, costs and consequences. Subsequently a trial-based cost-effectiveness analysis will be undertaken from an NHS/personal social services (PSS) perspective to determine the cost per percentage achieving TH of GH − compared to GH + over a 12-month period.

Resource use information will be obtained on all healthcare utilisation (primary care and secondary care) and will be obtained mainly from participant questionnaires. Unit costs will be obtained from standard sources and healthcare providers including the British National Formulary (BNF), PSSRU publication on Unit Costs of Health and Social Care and NHS Reference costs.

Mean costs and outcomes will be estimated for both the no GH therapy (GH −) and GH therapy (GH +) arms. Cost data are likely to be skewed; therefore, non-parametric comparison of means (e.g. bootstrapping) will be undertaken. Multiple imputation techniques will be used to deal with missing costs, in order to ensure that all eligible trial participants are included in the analysis.

Incremental cost-effectiveness ratios (ICERs) will be calculated, and cost-effectiveness acceptability curves will be presented to estimate the probability that GH − is cost-effective for different willingness to pay thresholds.

The second objective of the health economics analysis is to determine the cost-effectiveness of the new care pathway (early re-testing) compared to traditional care (late re-testing) using a decision analytic modelling approach. The model will determine the cost per percentage achieving TH and cost per additional quality-adjusted life year (QALY) gained for the intervention (early re-testing) and usual care arm (late re-testing).

Data from the main trial and other published sources will be used to populate the model. An incremental cost-effectiveness analysis will determine the cost per percentage achieving TH and an incremental cost-utility analysis will be undertaken to estimate the cost per QALY gained. Both analyses will be conducted from an NHS perspective. Deterministic sensitivity analysis will be undertaken to assess the impact of changing the values of key parameters. Uncertainty in the confidence to be placed on the results of the economic analysis will be explored by conducting a probabilistic sensitivity analysis to estimate cost-effectiveness acceptability curves.

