## Background

Around 500 children are diagnosed with growth hormone deficiency (GHD) every year in the UK, of whom 75% have idiopathic, isolated GHD (I-GHD) [1]. Children are treated with daily growth hormone (GH) injections until final height (FH) is reached, at an annual cost of £10,000–£23,000 per child [2]. However, when these children are re-tested after having reached their FH, between 64 and 82% are found to be producing sufficient endogenous GH [3–16], i.e. their GHD has reversed. Children with a normal pituitary on brain MRI and partial GHD are more likely to reverse. However, it is not unusual for children with structural abnormalities of the pituitary gland to also reverse [10, 12]. The underlying reasons for this reversal are largely unknown but may be explained by (1) late maturation of the GH axis or (2) difficulties inherent in the original diagnostic process.

To make the diagnosis of I-GHD in a short child, the National Institute for Health and Care Excellence (NICE) recommends at least two GH stimulation tests. These tests measure the peak GH concentration in the blood following an injection with a stimulating substance such as glucagon or insulin, and I-GHD is diagnosed if both show a peak GH < 6.7 μg/L [formerly 20 mU/L] [17]. However, a large number of GH stimulation tests are used in routine practice, and there is no consensus as to which is optimal for either diagnosing GHD or predicting a later GHD reversal [18]. Diagnostic test protocols also vary between institutions.

A number of studies have shown that sex steroid priming improves the response to provocative testing [19–21]. However, sex steroid priming is by no means universally used [22]. Additionally, studies have shown that the peak GH response is inversely correlated to weight within a cohort of normal weight children [23]. This study by Stanley et al. suggested that even normal children with a weight of + 1SDS may show a blunted GH response. Given all of these variables, it may not be surprising that the GH stimulation test itself could be associated with a high false positive rate and that re-testing after a suitable period, or at the end of GH treatment, may produce normal results, implying a reversal of GHD. This may be due to an effect of sex steroid or perhaps even loss of weight and improved body mass index.

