#### Planned interventions

Participants in the control arm (GH +) will resume receiving their GH treatment at a dosing level determined by their clinical care team (following the minimum 6-week discontinuation period required prior to randomisation). Participants in the experimental arm (GH −) will not resume GH treatment. Both arms will be followed up at 6 monthly intervals until near FH or the 36-month follow-up (whichever is soonest).

All currently available GH treatment preparations with the active ingredient Somatropin are allowed, as detailed in the British National Formulary for Children (BNFc) in the UK and Kindermedika in Austria (https://kindermedika.at/monographie/10222/somatropin).

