**Fig. 2 Fig2:**
[figure not shown]
GHD Reversal Trial schedule of assessments. Three asterisks (***) indicate the following: patients will be followed up until ‘Near FH (growth rate < 2 cm/year and bone age of 14 and 16 for males and females respectively). Given the usual duration of pubertal growth until FH is reached, 3 years follow-up has been allowed for; however, if patients do not reach near FH by 3 years, this may be longer

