#### Study procedures

Routine retesting in established puberty is routine clinical practice in all trial sites. Children with GHD persistence at retesting will restart GH; those with GHD reversal will be offered study participation. Following consent, participants will be randomised to GH + (25–35 µg/kg/day) and GH − groups and followed in routine endocrine clinics until ‘Near FH’ (growth rate < 2 cm/year) is reached. In the GH − group, any unexpected decrease in IGF-1 concentrations below − 2 SD (lower limit of normal) at 6 months would trigger a repeat GH stimulation test and recommencement of GH if deficient.

The baseline visit for all patients will include confirmation of inclusion and exclusion criteria, informed consent/assent, randomisation and allocation of trial number, prescription of growth hormone (if randomised to continue treatment), a record of the preparation and dose prescribed, a record of concomitant medication and relevant medical history. Height, weight and Tanner stage will also be measured at baseline. All patients will have 6-monthly visits to measure height, weight, Tanner stage, serum IGF-1 (at 6 months and annually thereafter) as well as checking compliance with GH therapy and any concomitant medication and adverse event reporting. HRQoL will be measured using the CHU9D questionnaire at baseline and at each 6-monthly visit. A left hand X-ray will be conducted at enrolment and near FH, for central analysis using the BoneXpert software. Fasting lipids will be measured at baseline and near FH.

At near FH, all subjects will have a GH stimulation test to reconfirm GH status. Given the usual duration of pubertal growth until near FH is achieved, we have allowed for 3 years follow-up.

The information captured at the randomisation and subsequent visits are shown in Fig. 2.

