#### Sample size and power calculation

Determination of non-inferiority margin was carefully considered, following extensive consultation. A questionnaire was sent to all investigators, British Society for Paediatric Endocrinology and Diabetes clinical study group members, and a patient support group representative (*n* = 34), giving several options for ‘acceptable deficit’ in various FH outcomes. These FH outcome options for comparison between the GH + and GH − groups were (1) the percentage of children reaching normal adult height (0 ± 2SD), (2) the percentage of children reaching mid-parental TH (0 ± 2SD) and (3) the near FH (in SDS/cm). Near-FH standard deviation score (near FH-SDS) was selected as the primary outcome.

Whilst the percentage of children reaching mid-parental TH [26] was the most popular outcome amongst respondents, data were not available to inform a sample size calculation. However, all the above options to express FH will be analysed in this trial as secondary outcomes. Other secondary outcomes are HRQoL, lipid profile, cost-effectiveness, and the bone health index (assessing effect of GH + /GH − on bone accrual and bone age using BoneXpert software).

For the primary outcome measure of near FH-SDS with a non-inferiority design comparing means and assuming equal variance, a non-inferiority margin of 0.55 near FH-SDS, a one-sided test with alpha = 0.025 and 90% power, a group size of 57 (total *n* = 114) would be needed (calculated using the SSI procedure in Stata 13). This calculation was based on a near FH-SDS (SD) of − 1.6 (0.9) using data from a population-based registry for patients with idiopathic GHD treated with GH and completing the scheduled treatment [27]. The non-inferiority margin is based on clinical opinion. Additional observational studies gave consistent results. Using the LMS growth software, a 0.55 height SDS score (using British 1990 Growth Charts [28]) approximates to 3.8 cm for boys and 3.3 cm for girls at age 23. With 17% allowance for withdrawal and loss to follow-up, a total sample size of 138 is required.

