## Discussion and potential impact

Five previous studies have demonstrated reversal of GHD (mean 49%; range 19–95%) with earlier re-testing, before or during puberty [4–6, 15, 16]. One study found that children with GHD reversal confirmed during puberty reach their target height (TH) without further GH therapy [6]. Another study showed that children stopping GH 1.6 years before attaining FH achieve a similar FH to those who continue taking GH until they reach their FH [30]. A GH stimulation test is usually performed when FH is attained to assess any requirement for adult GH therapy, and it is at this point that many patients are found to be no longer GH deficient. This study will test whether the near FH of those stopping GH treatment is not inferior to the near FH of those continuing and is thus the first study to our knowledge that is a randomised controlled trial. If this study shows that a significant proportion of children with I-GHD generate enough GH naturally in early puberty to reach a near FH within the target range, this new care pathway could rapidly improve practice; it would relieve patients from the diagnostic uncertainty of GHD persistence and may allow patients to stop GH therapy approximately 3 years earlier, and still reach a normal near FH without the burden of daily injections, and at considerably reduced health care cost. Based on published data, we can assume that on a 50% reversal rate, the potential cost savings for the NHS would be in the range of £1.8–4.6 million (€2.05–5.24 million)/year in drug costs alone [2]. It is important to note that GH treatment is not without its problems. Previous studies have suggested rare side-effects including benign intracranial hypertension, diabetes and slipped femoral capital epiphysis in association with GH treatment [30]. However, more recent data have suggested significant risks potentially associated with GH treatment. In those patients with normal GH secretion who were treated with high doses of GH, a higher incidence of bone tumours was reported [32]. Additionally, further data from the SaGHe study have revealed an increased incidence of cerebrovascular events in patients who previously received GH treatment [33]. However, more recently, detailed registry reviews indicated no increased risk of strokes or cancer, once risk factors had been accounted for [34]. Nonetheless, some controversy remains around safety of GH therapy, and it would be important to ensure that GH should only be considered in those patients who would benefit from its use, with a view to minimising any adverse effects.

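### The trial-based cost per percentage achieving target height is set over 12 months, but target-height attainment is settled at near final height, for which the plan allows about 3 years

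*Protocol article*

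**What the plan says.** The Health economics analysis section gives the 12-month period twice. The first aim is the cost per percentage of children achieving TH, GH− versus GH+, "over a 12-month period, and the second is to assess the cost-effectiveness of the new care pathway". The description of the trial-based analysis repeats it: the purpose is "to determine the cost per percentage achieving TH of GH − compared to GH + over a 12-month period". ICERs and acceptability curves follow from that analysis.

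The Health economics entry under Sub-studies states the same objective with no time limit.

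TH attainment is a final-height outcome. The Sample size and power calculation section names reaching mid-parental TH as one of three ways to express FH and says that "all the above options to express FH will be analysed in this trial as secondary outcomes". It is listed again among the growth-related secondary outcomes.

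On timing, Planned interventions has 6-monthly visits to near FH or 36 months, whichever comes sooner. Study procedures says "Given the usual duration of pubertal growth until near FH is achieved, we have allowed for 3 years follow-up", and the note to Fig. 2 adds "if patients do not reach near FH by 3 years, this may be longer". Planned final analyses defines near FH by a growth rate below 2 cm/year together with a bone-age threshold.

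On cost, the Background says that children are treated "until final height (FH) is reached, at an annual cost of" £10,000–£23,000 per child. The Discussion says that early re-testing "may allow patients to stop GH therapy approximately" 3 years earlier.

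**The concern.** A cost-effectiveness ratio needs its costs and its effect on one time horizon. Here the effect is settled when growth is nearly complete, and the stated period ends well before the time the plan allows for that. The article does not say how the two are joined, and neither way of joining them gives a sound ratio.

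- If costs and effect both stop at 12 months, TH status is not yet known for most children, so the effect side is largely missing.
- If costs stop at 12 months and TH is taken at near FH, the effect is observed. However, GH+ children go on incurring drug cost after month 12, and that cost is left out.

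Cost-effectiveness of GH− is part of the trial's stated Aim B. A non-inferiority conclusion can coexist with a small deficit in TH attainment, and the reader would then want to know the saving per percentage point forgone. That figure depends directly on the cost horizon.

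**Working it through.** The 12-month period is a stated choice, so there is no plan figure to reproduce. The check is how much of the drug-cost difference it leaves out.

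**Inputs**
- Annual GH cost per child, c: £10,000–£23,000 (Background).
- Cost window: 12 months (Health economics analysis).
- Time from randomisation to near FH, T: 3 years allowed for (Study procedures), about 3 years of GH saved (Discussion and potential impact). No distribution is given, so T is varied.

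**Assumptions**
- Constant yearly cost in GH+.
- GH+ children take GH until near FH.
- No GH restarts in GH−.

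**Formulas, for T of 12 months or more**
- Drug-cost difference to near FH = c × T/12
- Part outside the window = c × (T − 12)/12
- Omitted share = 1 − 12/T

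| T (months) | Difference to near FH | Outside the 12-month window | Omitted share |
|---|---|---|---|
| 18 | £15,000–£34,500 | £5,000–£11,500 | 33% |
| 24 | £20,000–£46,000 | £10,000–£23,000 | 50% |
| 30 | £25,000–£57,500 | £15,000–£34,500 | 60% |
| 36 | £30,000–£69,000 | £20,000–£46,000 | 67% |
| 42 | £35,000–£80,500 | £25,000–£57,500 | 71% |

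The 42-month row applies only if follow-up runs past 3 years, as the Fig. 2 note allows.

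**Discounting.** At an assumed 3.5% a year (the article gives no rate), the three-year factor is 1 + 1/1.035 + 1/1.035² = 2.90. The difference at 36 months becomes £29,000–£66,700, and the omitted share is 1 − 1/2.90 = 65.5%. Discounting hardly changes the result.

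**Effect on the ratio, for illustration.** Assume TH attainment is 5 percentage points lower in GH−. Counting drug cost only:
- 12-month costs: £10,000/5 to £23,000/5 = £2,000–£4,600 saved per child per point forgone.
- 36-month costs: £30,000/5 to £69,000/5 = £6,000–£13,800.

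The 5 points are an assumption and are not taken from the article.

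**The case against.** Several stronger readings are tempting, and the article does not support them.

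- **That TH attainment cannot be observed within 12 months at all.** Follow-up ends at near FH if that comes early. Entry extends to girls of 15 and boys of 17, and to stage B3 or 9–12 ml testes. Some children could reach near FH within a year, so the claim holds for most participants and not for all.
- **That the effect will be missing from the final data.** Planned final analyses places the other outcome analyses at the last participant's 36-month assessment, so TH data should be in hand by then. The difficulty is the stated period, which leaves open which of the two readings applies.
- **That two-thirds of the saving is lost, a threefold understatement.** This needs a full 36 months of GH in every GH+ child, while Planned interventions makes 36 months an upper limit. Study procedures also provides for restarting GH in GH− in some circumstances, which would shrink the absolute difference. Drug cost is only part of the planned cost measure, which takes in all primary and secondary care use.
- **That everything under the economic aim is wrong.** The early-versus-late re-testing comparison uses a separate decision model with its own acceptability curves and no stated 12-month limit. It does not repair the trial-based ratio, because it answers a different question. It does draw partly on trial data, so cost collection limited to one year could reach it indirectly.

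It is also fair to say that cutting costs at 12 months works against GH−, so it would not create a favourable result for the experimental arm. The economic analysis is confined to UK patients, and the primary outcome, the sample size and the non-inferiority conclusion do not depend on it.

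What survives is the mismatch. The 12-month period is explicit and repeated, so it is not a detail left to a fuller document, and it conflicts with the follow-up sections and with the sub-study summary.

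**Conclusion.** The concern holds for the trial-based GH− versus GH+ ratio, and for the ICER and acceptability curves built on it. As written, that ratio either lacks its effect for most participants or sets truncated costs against a near-FH effect. In the second case the saving from stopping GH is understated. The omitted share of the drug-cost difference runs from 33% to 67% for near FH at 18 to 36 months, under the assumptions listed in the working. The upper figure matches the article's own planning time of about 3 years, but should be quoted as the result of that assumption and not as a measured loss. This is a should-fix point: it affects a stated aim and is corrected mainly by wording.

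**What to change.** Reconcile the Health economics analysis section with the Health economics sub-study summary, Planned interventions and Study procedures:

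1. Set the within-trial horizon from randomisation to near FH or end of follow-up, for both costs and TH attainment, using the same TH data as the clinical secondary outcome.
2. Count GH and other healthcare costs over that whole horizon, and state a discount rate for costs and outcomes beyond year 1.
3. If a 12-month view is still wanted, present it as cost-consequence only, with no cost-per-TH ratio.

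The cost is small but not nil. Visits every 6 months are already planned to the end of follow-up. However, Study procedures places the record of GH preparation and dose at baseline and lists compliance checks afterwards. The text gives no schedule for the resource-use questionnaires, and the Fig. 2 schedule is not reproduced in the copy reviewed. If dose records or questionnaires were planned for baseline or year 1 only, they must be extended to the last 6-monthly visit. The article reports no patients recruited at publication, so the change could have been made before any cost data were lost.
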